**Flow chart of the study design.**

### Participants

We will recruit participants through Australian organisations that work with SSAYA, mental health organisations, advertising via social, online and news media, and information sessions to community groups (including support groups for SSAYA, health professionals that work with SSAYA).

Inclusion criteria are: Australian resident, aged between 18 and 25 years, same-sex attracted (self-identify as gay, lesbian or bisexual), access to the Internet, mild to moderate psychological distress (Kessler-10 score between 16 and 21) and having depressive and/or anxiety symptoms (being eligible to receive tailored content for at least one anxiety or depressive symptom).

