### Intervention

To inform the development of the program, focus groups were conducted with SSAYA (aged 18 to 25 years) who discussed their experiences regarding their sexual orientation, their mental health needs and their preferences for support services. These data, along with expert review, informed the modification of existing online CBT-based prevention and treatment programs of the National eTherapy Centre. The program content was adapted to be suitable for integrated multiple symptom treatment. In addition, content was personalised for SSAYA, by using inclusive language and content (for example, use of pictures and videos depicting people in same-sex relationships), providing examples of stressors, unhelpful thoughts and beliefs and unhelpful behaviours unique to challenges associated with being same-sex attracted (for example, 'coming out', feeling accepted by heterosexual peers, fear of being assaulted for being gay), providing information on services specialising in supporting same same-sex attracted individuals, providing information on how self-esteem can be affected by being same-sex attracted (for example, through homophobia and internalised homophobia) and strategies to strengthen self-esteem and self-acceptance. Further refinement of the program was undertaken following usability testing, whereby SSAYA reviewed specific modules within the program and made recommendations for amendments to content. This feedback was incorporated where appropriate.

The *Out & Online* program was developed as a standalone resource that should complement face-to-face therapy, but in itself does not require the involvement of a health professional. The program contains seven brief modules containing mental health and wellbeing information and exercises based on CBT principles. The modules contain generic information and information and exercises specific for the symptoms participants endorse in an online assessment at pre-intervention, which screens for generalised anxiety, obsessions and compulsions, posttraumatic stress, specific fear, social anxiety and depressive symptoms. Some program content is also tailored for gender. It is recommended to participants that they spend an hour a week over eight weeks reading through the online modules and practising offline exercises. An eighth module on prevention and help for suicidal thoughts is accessible to all participants at all times.

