### Administration of assessments

Upon registering on the *Out & Online* website participants will complete baseline assessments (week 0). Automated Email prompts will be sent to participants asking them to complete online assessments at 8 and 20 weeks post-randomisation. In addition, while completing the online program, participants will be prompted by automated Email to complete a survey at weeks 2, 4 and 6 of the 8 week program. Table 1 shows the schedule of assessments for each time point.

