**Table 1 Tab1:** **Intended assessments and administration frequency**

Outcomes	Concept	Instrument	Items	Intervention group			Wait-list control group			
				Week 0	Week 8	Week 20	Week 0	Week 8	Week 20	Week 28
Primary	Depressive symptoms	Patient Health Questionnaire-9	9	x	x	x	x	x	x	x
	Generalised anxiety	Generalised Anxiety Disorder-7	7	x	x	x	x	x	x	x
	Panic	Panic Disorder Severity Scale	7	x	x	x	x	x	x	x
	Social anxiety	Social Phobia Inventory	17	x	x	x	x	x	x	x
	Obsessions and compulsions	Obsessive-Compulsive Inventory-Revised	18	x	x	x	x	x	x	x
	Posttraumatic stress	Posttraumatic Stress Disorder Checklist-Civilian Version	11	x	x	x	x	x	x	x
	Specific fear	Fear Questionnaire	16	x	x	x	x	x	x	x
Secondary	Psychological distress	Kessler-10	10	x	x	x	x	x	x	x
	Psychological functioning	*Out & Online* Symptom eScreener	7	x	x	x	x	x	x	x
	Internalised homophobia	Internalised Homophobia Scale-Revised	5	x	x	x	x	x	x	x
	Help-seeking attitudes	Attitudes Toward Seeking Professional Psychological Help Scale	10	x	x	x	x	x	x	x
	Life satisfaction	Satisfaction With Life Scale	5	x	x	x	x	x	x	x
	Locus of control	Multidimensional Health Locus of Control Scales-Form C	18	x			x			
	Wellbeing	Mental Health Continuum Short Form	14	x	x	x	x	x	x	x
Moderators	Demographic factors	*Out & Online* Demographic Questionnaire	24	x			x			
Treatment	Program satisfaction	Intervention Evaluation Questionnaire	14		x					
	Departure	Departure Questionnaire	9							

Note*:* in addition to the above schedule, the Kessler-10 will be administered at fortnightly intervals during program completion.

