### Primary outcomes

The primary outcomes being assessed are reduction in anxiety and/or depressive symptoms. Validated questionnaires will be used to measure generalised anxiety (Generalised Anxiety Disorder 7 [46]), panic (Panic Disorder Severity Scale [47]), obsessions and compulsions (Obsessive-Compulsive Inventory-Revised [48]), social anxiety (Social Phobia Inventory [49]), posttraumatic stress (Posttraumatic Stress Disorder Checklist-Civilian Version [50]), specific fear (the Fear Questionnaire [51]) and depressive symptoms (Patient Health Questionnaire-9 [52]). These measures are also being used to determine whether participants are eligible to receive specific symptom content in their tailored online program.

In addition, an online screening device (eScreener) was developed in 2011 to measure anxiety and depressive symptoms. This eScreener will be compared against the validated questionnaires in order to develop a shorter means of determining symptom content for the online program. Once the eScreener is validated future entry to the program will first involve an assessment of psychological distress (with the Kessler-10 scale; K10 [53, 54]), with alternate referral recommendations with people with little or very high distress, and then administration of the eScreener as the sole means of determining symptom relevant content.

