### Secondary outcomes

As each participant will receive a different number (between one and three) and combination of symptom content (out of generalised anxiety, panic, social anxiety, obsessions/compulsions, specific fear and depressive symptoms), the K10 [53, 54] will be used as a secondary outcome to evaluate progress at fortnightly intervals during the intervention, and at pre- and post-intervention. As research has revealed a strong association between K10 scores and a current Composite International Diagnostic Interview diagnosis of anxiety and affective disorders [54], this short scale is appropriate for the fortnightly progress evaluations and it will allow us to examine the influence of different program lengths and types on the main outcomes of interest.

Additional secondary outcomes will include life satisfaction (Satisfaction With Life Scale [55]), wellbeing (Mental Health Continuum Short Form [56]), internalised homophobia (Internalised Homophobia Scale-Revised [57]), help-seeking attitudes (Attitudes Toward Seeking Professional Psychological Help Scale [58]) and locus of control (Multidimensional Health Locus of Control Scales-Form C [59]). Demographic and background information will be collected at pre-intervention. Participants in the intervention group will also complete a program evaluation survey, which will include standard items regarding satisfaction with the online intervention.

Participants will have the option to 'opt-out' of the trial by clicking on a link on the website or automated Email and those that do this will be invited to complete a Departure Questionnaire which captures reason for opting out of the study.

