### Statistical analyses

All scales used in the analysis will be validated using confirmatory factor analysis and reliability analyses. The intervention and wait-list control group will then be compared in terms of baseline measures for symptoms, health behaviour and wellbeing as well as possible confounds such as accessibility/remoteness and gender. Two multi-level modelling analyses will then be conducted. In the first analysis, the intervention and control group will be compared in relation to pre, post and follow-up changes for symptoms, health behaviour and wellbeing. In this analysis, significance levels will be adjusted to reflect the multiple primary outcome measures. In the second multi-level analysis only the intervention group will be considered, with fortnightly changes in the K10 compared in terms of the specific symptom-based programs that were completed by each participant during the previous fortnight (or previously in their intervention).

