## Discussion

This paper describes the study protocol for the development and evaluation of a mental health prevention program for SSAYA. Despite having a higher incidence of mental health problems than adults 25 years of age or over [39], only 1 in 4 young people with mental health problems receive professional help and there is a shortage of trained health professionals available to help them [63]. If successful, this online intervention will represent a significant step forward in terms of prevention and early intervention of mental health problems in SSAYA, and addressing barriers associated with stigma and geographic, social and financial isolation. The anticipated strengths and potential limitations of this study are detailed below.

The proposed program is unique and sophisticated, not only in targeting the mental health needs of SSAYA but in tailoring the program content to gender and symptom profile. The personalisation of this program and online nature may help to make it more attractive and engaging for young people than traditional face-to-face alternatives. Moreover, the integrated nature of the intervention enables the simultaneous treatment of multiple mental health symptoms within one program. This is a unique feature of the program, streamlining health care for the young person, as well as acknowledging the uniqueness of each user. This is expected to be a particularly important outcome for SSAYA in rural or regional areas. We expect the findings will enhance our understanding of the impact of internalised homophobia on recovery-related outcomes. We also anticipate that the use of the control condition will enable greater insight into the unique contribution of this program compared to standard mental health and wellbeing services available to SSAYA.

Despite these strengths, three potential limitations of this study design should be acknowledged. Firstly, each participant with a different set of symptoms identified at pre-intervention assessment will get different intervention content due to their receiving content for a different number and combination of types of symptoms when they do the *Out & Online* program. The main comparison with the wait-list control group cannot take these different interventions into account but follow-up statistical analyses will target the efficacy of interventions for each symptom type in isolation and in combination with other symptom types using regression analyses.

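### Content eligibility is measured at week 0 in both arms, so the randomised comparison can take it into account; comparing arms on each scale without it may dilute the primary effects

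*Protocol article*

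**What the plan says.** The Discussion lists as its first limitation that participants receive different content, and states: "The main comparison with the wait-list control group cannot take these different interventions into account". The same sentence goes on to promise follow-up regressions of efficacy by symptom type, singly and in combination.

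Other sections describe how content is set:

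- **Intervention:** the tailored material is "specific for the symptoms participants endorse in an online assessment at pre-intervention".
- **Primary outcomes:** seven questionnaires are listed. Of these the article says: "These measures are also being used to determine whether participants are eligible to receive specific symptom content in their tailored online program".
- **Participants:** one inclusion criterion is "being eligible to receive tailored content for at least one anxiety or depressive symptom".
- **Table 1:** all seven primary scales are marked at week 0 in both the intervention and the wait-list columns. Administration of assessments places the week-0 battery at registration.
- **Secondary outcomes:** the K10 is introduced with the reason "As each participant will receive a different number (between one and three) and combination of symptom content".
- **Statistical analyses:** in the first multi-level model "the intervention and control group will be compared in relation to pre, post and follow-up changes for symptoms", among other outcomes. Content eligibility is not mentioned, and significance levels are to be adjusted for the multiple primary measures.

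**The concern.** A factor measured before randomisation in both arms can be used in a randomised comparison as a covariate, an interaction with arm, a pre-specified subset, or a way of defining each participant's outcome. Eligibility for a symptom's content is such a factor. The limitation therefore rules out an analysis that the trial's own data allow.

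Seven scales are compared between arms, while any one participant gets specific content for at most three symptom types. Each scale's contrast then averages people whose program addressed that symptom with people whose program did not. If the second group gains less, the contrast understates what the content does for those it was meant for, and power falls with it. The plan would also pass over a randomised estimate bearing on a question it raises itself: whether the content for each symptom type works.

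**Working it through.** **1. Is eligibility known in both arms?** The primary questionnaires decide eligibility (Primary outcomes), at pre-intervention (Intervention), and both arms complete them at week 0 (Table 1). Eligibility for at least one content type is an entry criterion (Participants), so it has to be evaluated for everyone before randomisation. It is therefore a baseline variable in both arms. Two limits apply. Content later completed exists only in the intervention arm. And the article does not say how content is chosen when more than three types qualify, so for such participants eligibility is known but the exact assignment follows only once that rule is written down.

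**2. The plan's own figure.** Sample size and power calculations gives 38 per condition for f(V) = .15, power .80, alpha .05. A group-by-time MANOVA with 2 groups and m = 3 time points, assuming a correlation of 0.5 between time points (the article gives none), has λ = N·m·f²/(1 − ρ) = 76 × 3 × 0.0225 / 0.5 = 10.26 on 2 and 73 df. Power is .809, and N = 76 (38 per arm) is the smallest even total that reaches .80. The figure reproduces, and it takes f = .15 to apply to everyone analysed.

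**3. Share targeted per scale.** With 1 to 3 types per person over 7 scales, the average share p lies between 1/7 = 14% and 3/7 = 43%. If only six types are in use, as each content list has it, the ceiling is 3/6 = 50%.

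**4. Dilution.** Let untargeted participants gain a fraction s of the on-target effect d. The all-participant effect is d × [p + s(1 − p)].

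Assumed inputs: d = 0.636 SD (0.64 rounded), p = 3/7, two-sample t-test, two-sided alpha .05 unadjusted. Eligible-only uses d = 0.636 with 100 × 3/7 = 42.9 per arm, or 30 × 3/7 = 12.9 per arm if 70% drop out.

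| Spill-over s | Effect over everyone (SD) | Power, everyone, 100 per arm | Power, eligible-only, 42.9 per arm | Power, everyone, 30 per arm | Power, eligible-only, 12.9 per arm |
|---|---|---|---|---|---|
| 0% | 0.636 × 0.429 = 0.27 | .48 | .83 | .18 | .34 |
| 25% | 0.636 × 0.571 = 0.36 | .73 | .83 | .28 | .34 |
| 50% | 0.636 × 0.714 = 0.45 | .89 | .83 | .41 | .34 |

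The advantage of restricting to eligible participants reverses between 25% and 50% spill-over. At alpha .05/7, an illustrative choice because the article names no adjustment method, the 0% row at 100 per arm becomes .22 against .58.

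**5. The same check on the plan's f = .15.** At p = 3/7 and s = 0, f over everyone is .15 × 3/7 = .064. With 76 completers, power is .21 over everyone and .42 among the eligible (n = 33). With 200 and no drop-out it is .49 against .86 (n = 86). At 76 completers the comparison is .34 against .42 with 25% spill-over, and .51 against .42 with 50%. The pattern is the same.

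**The case against.** The strongest case against is that nothing invalid is planned. The aim and hypotheses ask whether being assigned the program reduces anxiety and depressive symptoms, and comparing everyone randomised answers that. The limitation is openly declared and comes with follow-up regressions. The K10, collected in both arms at weeks 0, 8 and 20, is a common measure that does not depend on which symptom was targeted. Read as content completed, *cannot* is defensible. The modules also hold generic material, so some spill-over is likely.

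Much of this stands. The overall comparison is a valid package effect and should stay. The mitigation is real but partial: the regressions are secondary, the article does not say whether they use the wait-list arm, and the K10 is a secondary outcome rather than one of the primary symptom scales.

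A reader might infer three stronger things that the article does not support:

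- **That a working program would look null on every scale.** The 43% is an average, and eligibility may be uneven. If, as an assumption, 80% qualified on one scale, power there over everyone would be about .95 with 100 per arm even without spill-over.
- **That an eligible-only analysis is always more powerful.** At 50% spill-over it is not.
- **That the follow-up regressions must be split over all 63 combinations of one to three out of seven types** (7 + 21 + 35). A regression needs only about one indicator per symptom type.

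**Conclusion.** The point holds in a limited form. As a statement about eligibility, the *cannot* sentence is contradicted by the article's own design; it is true only of content completed. Dilution of the per-scale effects follows whenever untargeted participants gain less than targeted ones. How large it is cannot be settled from the article, which gives neither the share eligible per scale nor any figure for spill-over. Only the one-to-three-of-seven bound comes from the text. The 0.64 SD effect, the 3/7 share, the spill-over fractions and the correlation of 0.5 are assumptions. Under them the loss ranges from serious (.48 against .83) to none (.89 against .83). This is a change the plan should make to use its data better, not a fault that invalidates the main comparison.

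**What to change.** 1. Replace the *cannot* sentence with a statement that content completed has no wait-list counterpart, but eligibility at week 0 is known in both arms and will be used.
2. Keep the overall comparison of all randomised participants.
3. Apply the content rule, including how types are chosen when more than three qualify, to week-0 scores in both arms. In each scale's model add baseline eligibility for that content and its interaction with arm, and report the arm effect among eligible participants beside the overall effect.
4. Pre-specify one summary that compares the arms on each participant's mean standardised score over the one to three symptoms their baseline assigns. This keeps everyone randomised and does not depend on the amount of spill-over to untargeted symptoms.
5. Reconcile the content-type lists, since any such analysis needs a single list. Set against the seven primary scales, Study aims omits specific fear, Intervention omits panic, and Secondary outcomes omits posttraumatic stress.

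The cost is a little more analysis and wording, with no new data. Per-scale estimates among eligible participants will be less precise because they rest on fewer people.

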### Online multi-symptom mental health and wellbeing program development

Given the need for online interventions relevant to SSAYA we developed an online CBT intervention (the *Out & Online* program, http://www.outandonline.org.au) designed to reduce anxiety and depressive symptoms and enhance wellbeing in SSAYA aged 18 to 25 years. The program was made relevant to SSAYA by using inclusive language and content (for example, pictures and videos depicting people in same-sex relationships), applying some of the strategies to stressors unique to being same-sex attracted (for example, 'coming out', feeing accepted by heterosexual peers and enhancing self-esteem and self-acceptance in the face of homophobia and internalised homophobia), and providing information on support services specialising in supporting same-sex attracted individuals.

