### Wait-list control group

The intervention is being compared to a wait-list control group so that participants in this group have the opportunity to complete the program. Participants in the wait-list control group will receive access to the intervention program after a 20-week delay. They are able to access any other mental health and wellbeing services during this time.

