### Hypotheses

It is hypothesised that at the post-intervention (week 8) and follow-up (week 20) assessment stages, participants assigned to access the intervention immediately will have fewer anxiety and depressive symptoms than those assigned to the wait-list control group.

In addition, it is hypothesised that at post-intervention and follow-up participants allocated to the intervention group will have less psychological distress, reduced internalised homophobia, greater life satisfaction, wellbeing, greater perception of control over their health, and more positive help-seeking attitudes than participants in the wait-list control group.

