Secondly, participant drop-out is a potential challenge, particularly given the self-help nature of the intervention [64]. To enhance motivation, the program modules are deliberately brief and incorporate interactive exercises, videos, audios, pictures and downloadable tip sheets. Contact details are provided on the website in case of questions or technical details. To encourage survey completion automated Emails are sent to participants and they are required to complete the K10 every 2 weeks while in the program in order to regain access to content. Sample size and power calculations have taken into account potential attrition and a conservative intention-to-treat analysis will be complimented with a longitudinal multi-level analysis to ameliorate the effects of drop-out at follow-up.

A third potential limitation is that the intervention is being compared to a wait-list control group, whereby participants will be able to access alternate evidence-based mental health services, including CBT. Information will be collected from participants about mental health service usage and the potential impact of this on outcomes will be statically controlled for.

In summary, SSAYA are at greater risk of poor mental health outcomes compared to their heterosexual peers. The provision of a preventive online mental health and wellbeing program, tailored to the gender and symptoms of the participant, may provide a cost-effective, anonymous and flexible medium for improving mental health outcomes for these individuals.

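### Controlling outcomes for mental health service use, if this means use after randomisation and is applied to the main comparison, would replace the intention-to-treat effect with one that can be biased either way

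*Protocol article*

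**What the plan says.** The third limitation in the Discussion is that, under a wait-list comparison, "participants will be able to access alternate evidence-based mental health services, including CBT". The remedy follows directly: "Information will be collected from participants about mental health service usage and the potential impact of this on outcomes will be statically controlled for" (the adverb is evidently a slip for statistically). The section Wait-list control group sets the period of this access. Of participants waiting out the 20-week delay it says: "They are able to access any other mental health and wellbeing services during this time".

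Other sections bear on whether allocation can alter service use:

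- The program development section lists, among the program's features, "providing information on support services specialising in supporting same-sex attracted individuals", and the Intervention section repeats it.
- The Intervention section describes the program as a "standalone resource that should complement face-to-face therapy".
- The Hypotheses predict that, at weeks 8 and 20, the intervention group will show "more positive help-seeking attitudes than participants in the wait-list control group".

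On the analysis itself, Statistical analyses says that in the first multi-level model "the intervention and control group will be compared in relation to pre, post and follow-up changes for symptoms, health behaviour and wellbeing". It names service use in neither of its two models. The Discussion, under the second limitation, promises an intention-to-treat analysis together with a longitudinal multi-level one.

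**The concern.** Randomisation protects a comparison of everyone offered the program with everyone made to wait. A variable that arises after allocation is outside that protection. Service use during the trial has two features that make it a poor covariate.

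First, the program may change it. Part of the program's benefit could come through services that participants are led to use. Alternatively, wait-listed participants may seek more help because they are waiting. Adjusting for use removes whatever part of the offered-program effect runs through it.

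Second, people who seek services are plausibly more unwell. If allocation also affects use, then comparing arms at the same level of use compares groups that differ in unmeasured severity. This can create a difference where there is none, or hide a real one.

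At stake is the meaning of the trial's central estimate. The commitment is also loose enough that an adjusted and an unadjusted result could both be called the planned analysis.

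**Working it through.** **Which service use is meant.** The limitation concerns services that participants can reach while the comparison is running, and the wait-list section places this in the 20-week delay. Adjusting only for use before randomisation would not answer that limitation. Use after randomisation is therefore the natural reading, although the sentence gives no time point.

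**Whether allocation can change it.** The signposting, the help-seeking hypothesis and the role as a complement to therapy all make it plausible that the program raises use. Help-seeking prompted by the wait would work the other way. The document offers no data on either.

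**How the two estimates are related.** Regress the outcome on arm, with and without a yes/no indicator of service use. Let Δ be the proportion using services in the program arm minus that in the wait-list arm. Let γ be the coefficient of service use in the adjusted model. Least squares then gives exactly:

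adjusted effect − unadjusted effect = −γ × Δ

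The two agree if Δ = 0 (or if γ = 0). Otherwise the sign of the shift depends on both terms.

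**Illustration.** The plan has no figure to reproduce here, and every input below is an assumption. Each scenario simulates 2,000,000 participants. Negative values mean fewer symptoms, in SD units. Service use lowers symptoms by 0.4 SD or not at all. An unmeasured severity factor, where present, has a coefficient of 0.5 in both the use and the outcome equation.

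| Scenario | Use, wait-list → program | Direct effect | Unadjusted | Adjusted | Shift |
|---|---|---|---|---|---|
| A. Use helps, no shared severity | 27% → 50% | −0.30 | −0.391 | −0.300 | +0.090 |
| B. As A, program lowers use | 27% → 11% | −0.30 | −0.235 | −0.299 | −0.064 |
| C. Use has no effect, shared severity | 30% → 50% | 0 | 0.002 | −0.073 | −0.075 |
| D. As C, program lowers use | 30% → 14% | 0 | −0.001 | +0.060 | +0.060 |
| E. Use helps and shared severity | 30% → 50% | −0.30 | −0.381 | −0.374 | +0.007 |
| F. As E, program lowers use | 30% → 14% | −0.30 | −0.239 | −0.242 | −0.002 |
| G. As E, use equal in both arms | 30% → 30% | −0.30 | −0.302 | −0.302 | 0.000 |

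(Shifts were computed before rounding.)

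Checks by hand:

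- A: γ = −0.4 and Δ = 0.50 − 0.27 = 0.23, so the shift is 0.4 × 0.23 = +0.092.
- B: Δ = 0.11 − 0.27 = −0.16, so the shift is 0.4 × (−0.16) = −0.064.
- C: the implied γ is 0.075 / 0.20 ≈ 0.375. D: 0.060 / 0.16 = 0.375. Services look harmful although they do nothing, because sicker people use them.
- E and F: the two influences on γ nearly cancel, −0.4 + 0.375 ≈ −0.025, so the shift is close to zero.

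In E and F the adjusted estimate is close to the unadjusted one, but it does not recover the direct effect either: it differs from −0.30 by 0.074 in E (−0.374) and by 0.058 in F (−0.242).

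The planned analysis is a multi-level model with repeated measures, so sizes would differ. The reasoning carries over.

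**The case against.** The strongest reply is that the article does not say the main comparison will be adjusted. Statistical analyses leaves service use out of both models, the commitment stands alone in a limitations paragraph, and an intention-to-treat analysis is promised just before it. The first limitation is met by follow-up analyses outside the main comparison, so this one might be too. This stands. A reader might infer that the primary estimate is certain to be conditioned on later service use, but the document supports only that it may be.

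A second reply is that bias needs allocation to change service use, and that mediation and shared severity can offset each other. This also stands. Scenario G shows no shift, and E and F show shifts below 0.01 SD. That cancellation depends on the assumed values, however, and the trial data could not confirm it.

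A third reply is that the Discussion wants to know what the program adds compared with standard services, so accounting for other care is a fair question. It is, but that is a different estimand. It needs the assumption that nothing unmeasured drives both service use and outcome, which randomisation does not supply.

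A reader might also infer from Table 1, which lists no service-use instrument, that the data will not exist. The article states that usage will be recorded, and an itemised schedule is detail that an article commonly condenses. No finding rests on it.

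**Conclusion.** The point holds in conditional form. The article commits to controlling outcomes for service use without restricting this to baseline use, naming the model or calling it supplementary. On its natural reading this is a post-randomisation variable that allocation could change. If it enters the main between-group comparison, the result is not the intention-to-treat effect and can be biased in either direction.

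The size cannot be stated, because no usage rates are given. The scenarios above moved the estimate by 0 to 0.09 SD, and those figures rest wholly on the assumed rates, service effect and severity link. A reader might infer a definite overstatement or understatement of the program's effect. The document supports neither, and there is no bias from this source if allocation leaves service use unchanged.

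**What to change.** Replace the sentence in the Discussion, and carry the same statement into Statistical analyses:

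> The primary intention-to-treat comparison is not adjusted for mental health service use after randomisation. Service use at week 0 may be included as a covariate. Service use after randomisation is reported by arm. Any analysis that conditions on it is exploratory, and its assumptions are stated with the result.

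This keeps the question of other care in view and takes it out of the primary estimate. The cost is a change of wording and slightly more reporting work. Sample size, visits and randomisation are unaffected.
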